**Design:**

This is a randomized controlled trial. Female participants with BC who are scheduled to undergo mastectomy, including unilateral total breast or breast-conserving surgery plus axillary lymph node dissection, will be enrolled in this study. The intervention includes the following: 200 participants will be allocated using a 1:1:1:1 ratio to the A, B, C, and D groups, which have four different rehabilitation timelines for four phases of rehabilitation exercises. A therapist will evaluate the patient’s overall health and then adjust the training intensity before initiating training. The assessments include upper limb mobility, grip, limb circumference, postoperative drainage volume (PDV), and pain. The training will last for 12 weeks, and patients will undergo follow-up twice within 6 weeks after discharge. Outcomes include the following: Constant-Murley Score (CMS) is the primary parameter. European Organization Research and Treatment of Cancer Quality of Life Questionnaire-BR23 (EORTC QLQ-BR23), SF-36, range of motion (ROM), strength, grip, circumference, PDV, and pain are the secondary parameters. All enrolled subjects will be assessed at 1 day, 3 days, 1 week, and 2, 3, 6, 9, 12, and 18 weeks after the surgery.

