### Outcomes

#### Primary parameter

CMS is a method that records individual parameters and provides an overall clinical functional assessment of the shoulder, and it is sufficiently sensitive to reveal even small changes in shoulder function [27, 28]. The score consists of the following four domains: pain (1 item), activities of daily living (ADL; 3 items for activity level, i.e., work, sports, sleep; 1 item for hand positioning, i.e., rotation), mobility (4 items: forward and lateral abduction/elevation, external and internal rotation), and strength (1 item) [29]. Pain and the three items for the activity level of ADL will be obtained from the patient, which means that patients will be self-assessed, while all other items will be assessed by the physiotherapist. The method of assessment will consist of clinical examination plus patient interview. The complete assessment only requires 5–7 min to perform [30]. All items are easy to understand and not emotionally sensitive. The respondent burden is minimal. The assessment of retest reliability using the intraclass correlation coefficient is 0.80–0.96, which indicates that the items in each scale are highly correlated with one another compared with items of another scale [31].

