#### Secondary parameters

Quality of life (QOL) is a multidimensional, subjective construct that reflects physical, mental, and social health domains of patients [32]. The European Organization Research and Treatment of Cancer (EORTC) QLQ-BR23 questionnaire is one of the most available tools for assessing aspects of QOL for BC patients [33]. It contains 23 items divided into two functional scales, including body image and sexuality, and three symptom scales, including arm symptoms, breast symptoms, and systemic therapy side effects. This questionnaire has been found to have a high internal consistency for 4 out of 5 scales and well-known group discriminative ability [34]. The validity of the EORTC QLQ-BR23 has been internationally scrutinized and explored in many countries, which has ultimately confirmed the questionnaire’s validity in BC [35].

The SF-36 is a general brief self-report questionnaire that assesses health-related QOL. The SF-36 contains 36 items that measure eight multi-item variables, including physical functioning, social functioning, role limitations due to physical problems, role limitations due to emotional problems, mental health, energy and vitality, bodily pain, and general perception of health, and there is a single-item scale on health transition. The score of each item ranges from 0 to 100. For each variable, the item scores are calculated, and a higher score indicates a better health status [36]. The internal consistency of the variables in the SF-36 is assessed with Cronbach’s α statistic and test-retest reliability [37]. Studies have shown that the SF-36 is acceptable for patients, and it has a high level of internal validity and good test-retest properties [38].

The assessments of shoulder function and quality of life will be evaluated at 1 week, 3 weeks, and 9 weeks after surgery.

In addition, joint mobility, muscle strength, grip, circumference, PDV, and pain, the parameters of exercise intensity in the pre-assessment, will also be evaluated as outcomes. Assessment methods and principles are the same as those for pre-assessments.

Shoulder ROM and strength will be assessed at postoperative 3 days and 1, 2, 3, 6, and 9 weeks. Grip will be evaluated at postoperative 1 day, 3 days, and 1, 2, 3, and 6 weeks, and upper limb circumference will be assessed at postoperative 1 day and 3, 12, and 18 weeks. PDV, pain, and skin will be evaluated by interview and palpation at postoperative 1 day, 3 days, 1 week, and 2 weeks.

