CMS, EORTC QLQ-BR23, and SF-36 will be required to be completed during the follow-up sessions at 12 and 18 weeks after surgery. During the follow-up sessions, information related to clinical testing, laboratory testing, and adverse events will be collected and assessed. Patients will be followed up in the ward during chemotherapy, and it is supplemented by telephone or WeChat.

Figure 2 shows a diagram of the study design.

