### Data analysis

#### Sample size

By estimating the sample size of the k-group sample mean comparison in a completely random design, the improvement scores for the CMS of the four groups of patients at 84 days after treatment were 15, 16, 18, and 19, and the standard deviations were 2, 2.5, 2.5, and 3, respectively. The assumption was that *α* = 0.05 and 1-*β* = 0.9. After calculation using PASS software (11.0), a total of 164 patients were required to be treated, and a 20% loss rate was calculated. Each group required 50 patients [39].

The calculation formula was as follows:
$$ n=\frac{\psi^2\left[{\sum}_{i=1}^k\frac{S_i^2}{k}\right]}{\left[{\sum}_{i=1}^k\frac{{\left(\overline{X_i}-\overline{X}\right)}^2}{\left(k-1\right)}\right]}. $$

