### Statistical analyses

Analyses will be performed using SPSS statistical software (version 20.0) by a statistician in the Department of Rehabilitation Medicine, Zhongnan Hospital of Wuhan University. Data will be analyzed according to the “intention-to-treat” (ITT) principle. A two-sided significance level of 5% will be used for all analyses. If the experimental data satisfies the normal distribution and the homogeneity of the variance, one-way analysis of variance (ANOVA) will be performed for comparison among the 4 groups with respect to the CMS, EORTC QLQ-BR23, SF-36, ROM, strength, grip, circumference, PDV, and pain. If there is an overall difference, the Tukey method for multiple comparisons will be used to compare the differences between groups at each time point. The results of repeated measurement ANOVA testing at each time point in each group will be analyzed by repeated measures to observe the recovery of patients at different times after surgery. For data with irregular variance, variable transformation can be used after the Kruskal-Wallis *H* test.

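### CMS is sized at 84 days, but no visit is named primary and groups are compared at each time point at an unadjusted 5%, so the false-positive rate on the primary outcome is not held at 5%

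*Protocol article*

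**What the plan says.** - **Primary outcome.** The abstract says "Constant-Murley Score (CMS) is the primary parameter". The Primary parameter section describes the instrument: "CMS is a method that records individual parameters and provides an overall clinical functional assessment of the shoulder". Neither attaches a visit.
- **Visits.** The Secondary parameters section says "The assessments of shoulder function and quality of life will be evaluated at 1 week, 3 weeks, and 9 weeks after surgery". It then says that CMS and the two quality-of-life questionnaires "will be required to be completed during the follow-up sessions at 12 and 18 weeks after surgery". Taking shoulder function to mean CMS, there are five CMS visits: weeks 1, 3, 9, 12 and 18.
- **Sizing.** The Sample size section uses four mean CMS improvements "at 84 days after treatment", with α = 0.05 and power 0.9. No other place singles out a time for CMS.
- **Testing.** The Statistical analyses section says "A two-sided significance level of 5% will be used for all analyses". It plans a one-way ANOVA among the four groups for CMS and all other outcomes, and then: "If there is an overall difference, the Tukey method for multiple comparisons will be used to compare the differences between groups at each time point".
- **Repeated measures.** The repeated-measures ANOVA is described within each group, to follow recovery over time. It is not a gate for the between-group tests.

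**The concern.** The trial is sized for one test of its primary outcome, while the analysis rules allow up to five at full level and do not say which one answers the trial's question. Tukey's adjustment works across groups at a given visit and does nothing across visits, and no hierarchy or split of alpha is stated.

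Two things are at stake. The nominal 5% does not describe the risk of a false finding on the primary outcome. The stated power also belongs to a visit that the analysis section never singles out. The abstract hopes to establish an optimal timeline, so a chance difference at one of five visits could end up supporting a recommendation.

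**Working it through.** **1. The plan's own sizing figure.** Inputs from the Sample size section: means 15, 16, 18, 19; SDs 2, 2.5, 2.5, 3; α = 0.05; power 0.9; four equal groups.

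- Grand mean 17; sum of squared deviations 4 + 1 + 1 + 4 = 10.
- Mean variance (4 + 6.25 + 6.25 + 9)/4 = 6.375.
- Effect size f = √[(10/4)/6.375] = 0.626.
- The protocol's formula with large-sample ψ = 2.17: n = ψ² × 6.375/(10/3) ≈ 9 per group.
- Exact noncentral-F calculation: 11 per group, 44 in total, power 92.8%. With SD 3 in every group: 14 per group, 56 in total.

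The stated 164 (41 per group) is not reproduced. This is a separate matter and hardly affects the error rate below, which is nearly the same at 41 and 50 per group. What counts here is that the calculation covers one comparison at one time.

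**2. Reference value if the visits were independent.** 1 − (1 − 0.05)⁵ = 1 − 0.95⁵ = 22.6%.

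**3. Correlated visits.** Repeated scores on the same patient are correlated, which lowers the rate. The article gives no correlation, so a range is assumed. Null trials were simulated (20,000 per setting, four groups, five normally distributed visits with equal correlation ρ). At each visit:

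- ANOVA is significant if n × (variance of the four group means)/MSE > F(0.95; 3, 4n − 4).
- At least one Tukey pair is significant if (largest mean − smallest mean)/√(MSE/n) > q(0.95; 4, 4n − 4).

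Chance of at least one significant visit out of five:

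| ρ | ANOVA, 41 per group | ANOVA, 50 per group | ANOVA and a Tukey pair, 41 per group | ANOVA and a Tukey pair, 50 per group |
|---|---|---|---|---|
| 0.3 | 20.8% | 21.5% | 17.7% | 18.4% |
| 0.5 | 19.3% | 18.7% | 16.5% | 16.3% |
| 0.7 | 15.6% | 15.3% | 13.5% | 13.2% |
| 0.8 | 13.2% | 13.6% | 11.5% | 11.9% |
| 0.9 | 10.9% | 10.6% | 9.3% | 9.2% |
| 0.95 | 8.6% | 8.9% | 7.3% | 7.8% |

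If correlation decays from visit to visit (AR(1), 50 per group), the ANOVA rate is 20.4%, 17.5% and 12.7% at 0.5, 0.7 and 0.9. If only four visits are tested, for example because week 1 serves as the baseline for improvement, it is 16.5%, 13.2% and 11.8% at equal correlations of 0.5, 0.7 and 0.8.

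**4. After the change.** One named visit: 5%. Five visits at 1% each: at most 5 × 1% = 5% (1 − 0.99⁵ = 4.9% if independent). With the protocol's means and SDs, power of the week-12 ANOVA at the 1% level with 41 per group is above 99.9%. Those inputs do not yield 164, so a harsher case was also run. A common SD of 5.31 is what would make 41 per group give 90% power at 5%; with that SD, power at 1% is about 75% with 41 per group and 85% with 50.

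**The case against.** The best counter-argument is that the 84-day comparison is plainly the main one and the other visits only describe recovery. That is a natural reading, and 84 days can only sensibly mean week 12: all groups start training on the first day after surgery, so counting from treatment or from surgery differs by about a day. But neither the Outcomes nor the Statistical analyses section says so, and the latter treats all time points alike.

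Second, the ANOVA sentence names no time point; the phrase about each time point belongs to the Tukey step. If a single overall test were meant as a gate, the error under a complete null would be 5%. That reading stands as a possibility. However, a one-way ANOVA has no time factor, so a single test would have to be at one visit, which is again unnamed.

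Third, a multiplicity hierarchy is often left to the full protocol or SAP. That is fair for the detail. The point here is narrower: the stated rules, 5% throughout and comparison at each time point, do not match the visit that was sized.

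Some stronger readings are not supported:

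- A reader might infer that any one significant visit counts as success. No sentence defines success that way.
- A reader might see a conflict between the abstract's "patients will undergo follow-up twice within 6 weeks after discharge" and the week 12 and 18 sessions. The discharge date is not given and those sessions are six weeks apart, so no conflict is shown.
- A reader might call weeks 1 and 3 uninformative because resistance training has hardly begun. They can still inform the first aim, on active exercise from day 3.

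**Conclusion.** The point holds as a mismatch between the sizing and the testing rules. With a separate ANOVA at each of five CMS visits, the chance of at least one false-positive result is about 10–22% at correlations of 0.9 to 0.3 and about 8–9% at 0.95. Requiring a significant Tukey pair as well gives about 9–18% at 0.9 to 0.3.

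The figures rest on three assumptions: the between-visit correlation, which the article does not give; one omnibus test per visit; and normal data with equal variances. No single interval is a property of the plan. The direction is firm, since every correlation tried under this reading gives more than 5%.

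**What to change.** In the Primary parameter and Statistical analyses sections, state: the primary endpoint is CMS improvement at week 12 (84 days) after surgery, with the baseline for improvement named; it alone is tested at two-sided 5% among the four groups, with Tukey's method for the pairs. CMS at weeks 1, 3, 9 and 18 is secondary and reported as estimates with 95% confidence intervals, without confirmatory claims. In the Sample size section, write 84 days (week 12) after surgery so that it matches the visit schedule.

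If the sponsor wants all five visits to be confirmatory, test each at 1%, Tukey step included.

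The cost is one paragraph of wording. The downside of the first option is that significant results at other visits can no longer be claimed as primary. The second option loses almost no power on the protocol's means and SDs, but would lose a material amount if the true SD were near 5.3.

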### Aim of this study

The aims of this study are as follows:
Observation of the optimal active exercises of the shoulder joint under full evaluation at 3 days after surgery, with respect to whether it accelerates the recovery of shoulder function and improves the quality of life of postoperative patients with BC. Evaluation of whether early-stage rehabilitation training leads to an increase in PDV, which affects shoulder function and the time of extubation in BC patients.Observation of progressive resistance training (PRT) in the case of full evaluation at 3 weeks after surgery, with respect to whether it promotes the recovery of shoulder function.

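### No named analysis tests whether the course of recovery differs between the four timelines, and the named ANOVAs fit poorly with ITT when 20% loss is expected

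*Protocol article*

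**What the plan says.** All of this is in the Protocol article.

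- **Aim of this study.** For active exercise from day 3, the question is "whether it accelerates the recovery of shoulder function". A parallel aim covers resistance training from week 3.
- **Statistical analyses, principle.** "Data will be analyzed according to the “intention-to-treat” (ITT) principle".
- **Statistical analyses, between groups.** "one-way analysis of variance (ANOVA) will be performed for comparison among the 4 groups with respect to the CMS" and the other outcomes. If the overall test is positive, "the Tukey method for multiple comparisons will be used to compare the differences between groups at each time point".
- **Statistical analyses, over time.** "The results of repeated measurement ANOVA testing at each time point in each group will be analyzed by repeated measures to observe the recovery". No group-by-time term is named.
- **Sample size.** CMS improvements at 84 days of 15, 16, 18 and 19 points, with SDs 2, 2.5, 2.5 and 3; 164 patients, then "a 20% loss rate was calculated", giving 50 per group.
- **Secondary parameters and the follow-up text after it.** CMS is scheduled at weeks 1, 3, 9, 12 and 18, five visits in all.

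**The concern.** Whether one timeline accelerates recovery relative to another is a between-group question about change over time. The longitudinal analysis, as worded, looks at change over time inside each arm. The between-group analysis looks at one visit at a time. Neither tests whether the four recovery curves differ.

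The second issue is who enters these analyses. Unless values are imputed, a one-way ANOVA at a visit includes only patients measured at that visit, and a classical repeated-measures ANOVA only those measured at all visits. The plan promises ITT and allows for losing a fifth of patients. If loss depends on how a patient was doing earlier, and does so differently by timeline, means of the remaining patients no longer compare the groups as randomised.

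**Working it through.** **1. Do within-group time effects carry information on which timeline is faster?**
Take the planned gains and SDs, reading the SDs as those of the gains, and 40 patients per group after 20% loss (50 × 0.8). The expected test statistic is gain / (SD/√40):

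| Group | Gain | SD | Statistic |
|---|---|---|---|
| A | 15 | 2 | 47.4 |
| B | 16 | 2.5 | 40.5 |
| C | 18 | 2.5 | 45.5 |
| D | 19 | 3 | 40.1 |

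Every arm shows overwhelming improvement. The slowest planned arm (A) has the largest statistic and the fastest (D) the smallest. Within-arm significance does not order the timelines.

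**2. How many patients does an all-visits analysis keep?**
The plan's own figures: 164 × 1.2 = 196.8 and 164 / 0.8 = 205, so 200 is a fair rounding of a 20% allowance. (The 164 itself was not reproduced from the stated inputs; that is a separate matter and does not bear on this point.) Taking the 20% as lost before the last visit leaves 200 × 0.8 = 160. The protocol gives no rate of missed visits among those retained, so the rates below are assumptions, with visits missed independently:

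| Missed per visit | Share with all five | Of 160 |
|---|---|---|
| 2% | 0.98^5 = 0.904 | about 145 |
| 5% | 0.95^5 = 0.774 | about 124 |
| 10% | 0.90^5 = 0.590 | about 94 |

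A one-visit ANOVA loses only those absent at that visit.

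**3. Does this threaten power?**
No, for the overall test. The common SD is √((4 + 6.25 + 6.25 + 9)/4) = √6.375 = 2.525. One-way ANOVA at the planned means has power above 0.999 with 40, 31 or even 23 per group (94/4 is about 23). This says nothing about the pairwise contrasts.

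**4. How large could bias be?**
An illustration under assumptions only. In one arm, the 20% lost are exactly those with the worst scores at an earlier visit; in the comparison arm, loss is random. Scores are normal, with correlation r between the earlier visit and week 12.

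- Mean of a standard normal above its 20th percentile: 0.280 / 0.8 = 0.350.
- Bias at week 12 = 0.350 × r × 2.525.
- r = 0.4, 0.6, 0.8 gives 0.35, 0.53, 0.71 points, in favour of the arm that lost its worst patients.

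The planned pairwise gaps are 1 (A–B, C–D), 2 (B–C), 3 (A–C, B–D) and 4 (A–D). The bias is therefore 35–71% of a 1-point gap, 12–24% of a 3-point gap and 9–18% of the 4-point gap.

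Simulating this pattern with 50 per arm gave complete-case bias of 0.35, 0.52 and 0.70. A likelihood estimate that also uses the earlier score of those lost had bias of 0.01 or less.

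**The case against.** **The timelines are compared.** A reader might infer that the plan never compares recovery between groups. It does: ANOVA and Tukey at each time point set randomised groups against each other, and a difference at an early visit is evidence on speed. This stands. What is missing is a test that the courses differ, not any comparison at all.

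**An ANOVA on improvement scores would be a group-by-time contrast.** For a single visit that is right, and the sample size is framed in improvement. But the analysis section names CMS, not its change, and the first scheduled CMS is at week 1, after groups C and D have started phase 2 on day 3. Change from week 1 would not be change from an unexposed baseline.

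**The within-group analysis is descriptive.** Its stated purpose is to observe recovery. Nothing says that within-group p-values will be used to rank timelines, and that use should not be attributed to the plan. The sentence is also garbled, so a model with group as a between-patient factor is not excluded. That is a reason to rewrite it.

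**The plan does not say that incomplete patients are dropped.** This stands too. Exclusion is how the named methods behave without imputation. Missing-data rules are often left to an analysis plan, and none is shown here. A reader might call this a contradiction of ITT; the text supports only a tension.

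**The bias figure is an extreme.** It needs loss of exactly the worst fifth in one arm and random loss in the other. Nothing in the protocol predicts that, and random loss alone would not bias the means.

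**Conclusion.** The point holds in limited form. No analysis named in the protocol tests whether the course of CMS differs between the four timelines, although an aim asks this. The named methods, used without imputation, sit uneasily with ITT when 20% loss is expected.

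The first conclusion rests on the natural reading of an unclear sentence. The second rests on the default behaviour of the methods, not on a stated exclusion rule.

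On size, power of the overall test stays above 0.999 under the planned inputs. Bias of about 0.35 to 0.71 points in one pairwise week-12 comparison is possible under the assumed one-sided selection and correlations of 0.4 to 0.8. It is an illustration of scale, not a forecast. It matters most for the 1-point gaps. Quoting only the 35–71% share would overstate it, since the other planned gaps are 2 to 4 points.

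**What to change.** For CMS, replace the separate per-visit ANOVAs and the within-group repeated-measures ANOVA with one linear mixed model.

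- **Patients:** all randomised patients with any CMS value, in the group assigned.
- **Terms:** group (four levels), visit (weeks 1, 3, 9, 12, 18) and group-by-visit, which has 3 × 4 = 12 degrees of freedom; unstructured covariance within patient.
- **Primary:** Tukey-adjusted between-group contrasts at week 12, matching the 84-day basis of the sample size.
- **Speed of recovery:** the group-by-visit test and the contrasts at earlier visits.
- **Week-1 CMS:** an outcome, not a baseline covariate, because groups C and D have begun phase 2 by then.

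Keeping group at four levels preserves the comparison the trial planned. Recasting it as two timing factors would be a separate decision and is not needed here.

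The cost is a rewritten paragraph and modest programming in the planned package (SPSS 20.0), with no new patients, visits or data. The downside is that the model assumes data are missing at random given the scores already observed, and this should be stated. Patients with no CMS value at all still contribute nothing.

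### Kruskal-Wallis with a later transformation does not deal with unequal variances, and the protocol's own planning SDs make that branch likely for the primary outcome

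*Protocol article*

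**What the plan says.** The Statistical analyses section sets a conditional rule for CMS and for every listed secondary outcome: "If the experimental data satisfies the normal distribution and the homogeneity of the variance, one-way analysis of variance (ANOVA) will be performed" to compare the four groups. Pairwise testing follows a significant overall result: "If there is an overall difference, the Tukey method for multiple comparisons will be used", at each time point. The section ends with the fallback: "For data with irregular variance, variable transformation can be used after the Kruskal-Wallis" H test. It names neither a test nor a threshold for judging equality of variances. The level is fixed by "A two-sided significance level of 5% will be used for all analyses".

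The Sample size section gives the planning values for the primary outcome. The group means of day-84 CMS improvement are 15, 16, 18 and 19. On their spread it states that "the standard deviations were 2, 2.5, 2.5, and 3, respectively". It asks for 164 patients in total, raised to 50 per group for 20% loss. Allocation is 1:1:1:1.

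**The concern.** Three things look wrong.

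- **The fallback does not address its trigger.** Unequal variances send the analyst to a rank test. That test can be read as a comparison of location only if the groups share shape and spread, which is the condition that has just failed. It also yields no difference in CMS points.
- **The stated order has no useful effect.** A monotone transformation applied after a rank test leaves the ranks, and so the test, unchanged.
- **The protocol expects the trigger.** It plans the primary outcome with a largest-to-smallest variance ratio of 9/4 = 2.25, yet makes its main analysis conditional on equal variances.

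At stake is what the primary result will be: a comparison of mean CMS improvement or a rank p-value, decided by a preliminary look at the same data. When the check passes, Tukey's pooled variance is still applied to groups planned to differ in spread, and pairwise comparisons are how the trial would choose a timeline.

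**Working it through.** **Inputs.** From Sample size: SDs 2, 2.5, 2.5, 3, read in the order A to D; means 15, 16, 18, 19; 164/4 = 41 evaluable per group; 50 enrolled per group. Assumptions not in the protocol: normal data unless stated, and Levene's test at 5% as the variance check. The plan gives no figure of its own on this point to reproduce. (The stated 164 does not follow from these means and SDs by omnibus ANOVA, which needs 10 to 14 per group. That is a separate matter; the group sizes are used here as given.)

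**1. Transformation after Kruskal-Wallis.** The statistic depends on the data only through ranks. A strictly increasing function such as the log keeps the ranks, so the p-value is identical. In five simulated data sets the p-values were 0.335, 0.398, 0.232, 0.745 and 0.227 both before and after logging. Transforming first and then using Kruskal-Wallis gives the same result. A transformation followed by ANOVA is different: at the planned means and SDs, logging cuts Levene rejection at 41 per group from 48% to 17%. The fault is therefore the order and the choice of test, not transformation as such.

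**2. Kruskal-Wallis under unequal spread.** With skewed data (gamma, shape 2), equal means and the planned SDs, rejection at the 5% level was:

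| n per group | Kruskal-Wallis | Welch |
|---|---|---|
| 41 | 8.1% | 5.8% |
| 50 | 8.9% | 5.8% |
| 200 | 24% | 5.1% |

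**3. How often the fallback applies.** Share of 40,000 normal data sets, SDs 2, 2.5, 2.5, 3, in which equality of variances is rejected at 5%:

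| n per group | Levene, mean-centred | Levene, median-centred | Bartlett |
|---|---|---|---|
| 40 | 46.7% | 42.3% | 53.4% |
| 41 | 48.1% | 43.1% | 54.5% |
| 50 | 57.2% | 53.5% | 64.3% |

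With equal SDs, Levene rejects in about 5.5%. Allowing for variation between runs, Levene gives about 42-57% at 41-50 per group.

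**4. Pooled standard errors in Tukey.** The pooled variance is (4 + 6.25 + 6.25 + 9)/4 = 6.375. The pooled SE of any difference is √(2 × 6.375/n) = √(12.75/41) = 0.558 at n = 41. The true SE is √((s_i² + s_j²)/n). The ratio does not depend on n when groups are equal in size.

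| Pair | s_i² + s_j² | True SE | Pooled/true | Per-pair error, n = 41 |
|---|---|---|---|---|
| A-B, A-C | 10.25 | 0.500 | 1.115 | 0.4% |
| A-D | 13.00 | 0.563 | 0.990 | 1.05% |
| B-C | 12.50 | 0.552 | 1.010 | 0.95% |
| B-D, C-D | 15.25 | 0.610 | 0.914 | 1.75-1.86% |

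The last column comes from 20,000 simulated trials with equal means; with equal SDs it would be about 0.96% for every pair. Across runs at 40-50 per group, B-D and C-D lie at about 1.5-2.2%, and A-B and A-C at 0.3-0.5%. Keeping only trials that pass Levene does not remove the imbalance.

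**5. Overall error.** With normal data and equal means at 41 per group, type I error is 5.3% for ANOVA, 5.2% for Kruskal-Wallis, 5.1% for Welch and 5.1% for the two-stage rule. Tukey's familywise error is 5.2%. At the planned means, all three overall tests reject in essentially every data set.

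**6. Worst-case reading of the fallback.** Suppose that, after Levene rejects, ANOVA on logged data is run as well and either significant result counts. With a common mean of 17, which is (15 + 16 + 18 + 19)/4, type I error is 6.2% at 40 per group and 6.8% at 50.

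**The case against.** The best defence is that little goes wrong under the protocol's own assumptions. Allocation is balanced, overall and familywise error stay near 5%, and at the planned means ANOVA and Kruskal-Wallis reach the same overall conclusion. Tukey is used only after a significant overall test; with that condition, C-D error falls to 1.5% at 40 per group and 1.9% at 50, and familywise error to 4.3% and 4.8%. Turning to Kruskal-Wallis when ANOVA assumptions fail is conventional, and the choice of variance test and transformation can be left to an analysis plan. All of this stands, and it limits the severity. It does not rescue the sentence, which states a rule that fails in either order.

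Stronger readings that the document does not support:

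- **A reader might infer that the plan licenses a second try at significance.** The sentence only says that a transformation can be used afterwards. It names no log transformation and no rule to report whichever test succeeds, and it may be a slip for a choice between transformation and rank test. The 6.2-6.8% is a worst case, not a stated rule.
- **A reader might infer that half of all analyses are affected.** SDs are given only for day-84 CMS improvement. Nothing can be said for SF-36, EORTC QLQ-BR23, range of motion, grip or drainage volume.
- **A reader might infer that the data will certainly fail the check.** The SDs are planning values and no check is named. With SDs of 2.25, 2.5, 2.5 and 2.75, rejection drops to 15-16%.

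**Conclusion.** The point holds in this limited form. The fallback is not a remedy for unequal variances on any reading of its order. If the planning SDs are right, CMS improvement is normal and Levene's test at 5% is the check, the form of the primary analysis is close to a coin-flip: about 42-57% of trials at 41-50 per group would leave ANOVA. In the rest, Tukey's SE is 8.6% too small for B-D and C-D (1/1.094 = 0.914) and 11.5% too large for A-B and A-C. A-B and C-D are two of the pairs planned to differ by only one point, so their precision matters.

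The harm is to what is estimated, to individual pairwise comparisons and to skewed outcomes. It is not a general inflation of type I error. Severity is minor to moderate.

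**What to change.** Delete the last sentence of Statistical analyses and the condition on equal variances. Prespecify Welch's ANOVA for the four-group comparisons of CMS and the other continuous outcomes, with Games-Howell pairwise comparisons reported as mean differences with confidence intervals. Keep Kruskal-Wallis only as a labelled sensitivity analysis on the untransformed outcome. If a transformation is wanted for a particular outcome, name it in advance and apply it before the parametric test.

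The cost is a few lines of wording, standard software options and a slight loss of power if the variances are in fact equal. At the planned SDs, Welch held type I error at 5.1% (41 per group) and 4.9% (50 per group), with power of about 1.00 at the planned means. Sample size and conduct do not change.
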